### 1.2.4 Clinical studies of the H56:IC31 TB vaccine

Three phase I clinical trials and two phase II clinical trials of SSI's preceding and structurally related vaccine candidate H1 (Ag85B/ESAT-6):IC31® have been conducted in humans demonstrating good safety and tolerability.

The first phase I trial with H56:IC31, an open-label, dose-escalation clinical study (C-032-456) in latent TB has just been finalized and show that the vaccine is immunogenic and well tolerated. Further, in C-035-456, a phase I/IIa randomized, placebo-controlled study of HIV-negative adults, no safety issues have been identified. In these trials a total of 123 subjects have been vaccinated, 25 of whom have received up to three doses of H56:IC31. The dose of H56:IC31 in these trials ranges from 5 to 50 µg H56 with 500 nmol IC31. Concerning immunogenic efficacy for Ag85B, the most prominent CD4+ responses at Study Day 70 were polyfunctional (IFN- $\gamma$ , IL-2, TNF $\alpha$ ), bifunctional (IL-2 and TNF $\alpha$ ), and monofunctional (IL-2). For ESAT-6, the most prominent CD4+ responses at Study Day 14 were polyfunctional (IFN- $\gamma$ , IL-2, TNF), bifunctional (IFN- $\gamma$  and TNF $\alpha$ ), and monofunctional (IFN- $\gamma$  or TNF $\alpha$ ). CD4+ cells expressing IL-17 were rarely present after stimulation with either antigen Ag85B or ESAT-6.

Thus, H56:IC31 was associated with an acceptable safety profile in subjects with and without LTBI, and no vaccine-related serious adverse events (SAEs) were reported. Vaccination with H56:IC31 was associated most commonly ( $\geq 10\%$  of subjects with a related adverse event) with mild to moderate injection site reactions of pain, warmth, and swelling; mild to moderate systemic adverse events of fatigue, bradycardia, myalgia, nausea, headache, arthralgia, and white blood cell count increased; and mild to severe hypertension. Only two SAE have been reported to date in clinical trials of H56:IC31, both considered not related to study vaccine. One serious AE, unrelated to study vaccine, was reported in the registry study. There are no reports of deaths due to vaccines containing similar fusion proteins (H1 and H4) to H56 or containing IC31 adjuvant.

A phase I/II clinical trial of H56:IC31 (C-037-456) in patients treated for active pulmonary TB has started in South-Africa in 2015, and no adverse events have been reported after the first 12 subjects have been vaccinated (by February 2015). The relationship between possible immune-related toxicities to the TB antigens and time since start of anti-TB chemotherapy will be addressed in C-037-456. The current study will await the inclusion of patients to the H56:IC31 arms until preliminary safety data from this trial is available.

In conclusion, all non-clinical and clinical information supports the suitability of H56:IC31 as a safe and immunogenic vaccine. There is no reason to believe that the combination of COX2i and vaccination is unfavorable.

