### **6.3.3 Rules for Discontinuing Vaccine Injections in an Individual Subject**

Administration of additional study injections will be discontinued for an individual subject if he/she has any of the following:

- An objective clinical or laboratory parameter change which meets Grade 3 or Grade 4 severity, as defined in the protocol toxicity table, AND is judged to be possibly, probably, or definitely related to study vaccine.
- Fever (oral temperature  $\geq 39^{\circ}\text{C}$ ) within 1 week following study injection which is associated with constitutional symptoms (myalgia, arthralgia, fatigue, headache, anorexia, hives, chills) AND is judged to be possibly, probably, or definitely related to study injection.
- Injection site reaction that involves severe induration ( $>10$  cm, prevents daily activity or necrosis/ulceration), erythema ( $>10$  cm or necrosis/ulceration/ exfoliative dermatitis), tenderness (significant discomfort at rest or study site visit or hospitalization) or pain (any use of narcotic pain reliever or prevents daily activity or study site visit or hospitalization).
- Any event that in the opinion of the principal investigator precludes administration of any further study injections.

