## 8.2 Expected Adverse Events (EAE)

**Etoricoxib**: Gastrointestinal EAE and headache are the most commonly occurring.  $\geq 1/100$  til  $< 1/10$ : abdominal pain, constipation, gastritis, reflux, gas, diarra, dyspeptic discomfort, nausea, vomiting, eosophagitis, palpitations, arrhythmia, hypertension, alveolar osteitis, increase in liver enzymes (ALAT/ASAT), bronchospasm, dizziness, headache, oedema, fatigue (text from Arcoxia, MSD, ATC-nr.: M01A H05 in Felleskatalogen). The EAEs will be recorded in the CRF.

**H56:IC31**: Vaccination with H56:IC31 has been associated most commonly ( $\geq 10\%$  of subjects with one or several of the AE) with mild to moderate injection site reactions of pain, warmth, and swelling, mild to moderate systemic adverse events of fatigue, bradycardia, myalgia, nausea, headache, arthralgia, and white blood cell count increased; and mild to severe hypertension (Table 5-8, page 72, Statens Serum Institut Investigator's Brochure).

There have been no suspected unexpected serious adverse reactions (SUSARs) reported to date in clinical trials of H56:IC31.

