## 8.6 Solicited Adverse Events and Injection Site Reactions

Solicited AE are events the subject is specifically asked about. These AE are commonly observed soon after receipt of vaccines. For this study, solicited AE to be collected include:

Local: injection site pain, injection site erythema, injection site swelling

Systemic: fatigue, myalgia, arthralgia, pyrexia, chills, nausea.

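### The solicited-event list in section 8.6 omits headache and injection-site warmth, both named elsewhere as common H56:IC31 reactions, so their capture is less systematic than for the listed reactions

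*Protocol*

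**What the plan says.** Section 1.2.4 describes earlier experience with the vaccine. The most common local findings were "mild to moderate injection site reactions of pain, warmth, and swelling", and the systemic ones were "mild to moderate systemic adverse events of fatigue, bradycardia, myalgia, nausea, headache, arthralgia, and white blood cell count increased". Section 8.2 repeats the profile under expected events, with the systemic part given as "mild to moderate systemic adverse events of fatigue, bradycardia, myalgia, nausea, headache, arthralgia, and white blood cell count increased; and mild to severe hypertension". For etoricoxib, the same section states: "Gastrointestinal EAE and headache are the most commonly occurring".

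Section 8.6 defines solicited events as those raised with the subject by direct question, and explains that they are events often seen soon after vaccination. It then gives two lines: "Local: injection site pain, injection site erythema, injection site swelling" and "Systemic: fatigue, myalgia, arthralgia, pyrexia, chills, nausea".

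Section 6.3.3 has a rule for stopping vaccine injections that refers to fever accompanied by "constitutional symptoms (myalgia, arthralgia, fatigue, headache, anorexia, hives, chills".

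Safety and tolerability are the primary objective (section 2). The statistical methods description makes the occurrence of adverse events the primary outcome.

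**The concern.** A solicited list makes sure that known reactions are looked for in every subject in the same way. Here the list was not brought into line with the protocol's own account of what the vaccine does. It includes injection-site erythema, pyrexia and chills, which are not in the common-reaction profile, and leaves out headache and warmth, which are. No reason is given.

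Headache matters most. It is expected for both products, it has its own row in the toxicity table, and 6.3.3 names it. Warmth has neither a place in 8.6 nor a row in the toxicity table, whose local rows are pain, tenderness, erythema and induration, so staff have no prompt to ask about it and no grade to give it.

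What is at stake is uniform recording of primary-outcome events. A direct question at each contact and a general adverse event inquiry do not find the same share of mild, short-lived symptoms, and section 8.6 itself recognises direct questioning as a separate method.

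**Working it through.** This is a comparison of lists; the plan has no figure to reproduce.

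Common H56:IC31 reactions in 1.2.4 and 8.2 (11 terms), set against 8.6:

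| Reaction | In 8.6 list? | Other scheduled measurement |
|---|---|---|
| Injection-site pain | Yes | Site examination |
| Injection-site swelling | Yes | Site examination |
| Injection-site warmth | **No** | Site examination, but no toxicity-table row |
| Fatigue | Yes | – |
| Myalgia | Yes | – |
| Nausea | Yes | – |
| Arthralgia | Yes | – |
| Headache | **No** | – |
| Bradycardia | No | Pulse at every visit |
| Hypertension | No | Blood pressure at every visit |
| White cell count increase | No | Haematology at every visit |

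- Common and solicited: 6 of 11. Common and not solicited: 11 − 6 = 5.
- Three of those five are measured at every visit and need no question. That leaves 11 − 3 = 8 reactions a patient could report, of which 6 are asked about and 8 − 6 = 2 are not: headache and warmth.
- Section 8.6 has 9 terms (3 local, 6 systemic). Since 6 of them match the profile, 9 − 6 = 3 are extra: erythema, pyrexia and chills.

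Symptoms named in the fever rule of 6.3.3: seven. Four are solicited (myalgia, arthralgia, fatigue, chills) and three are not (headache, anorexia, hives).

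Other ways in which the two events can be recorded:

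- Section 7.2 has adverse events collected at every visit. Section 8.5 covers events that the patient experienced or that staff saw. Section 7.2.7 alerts staff that headache may occur.
- Section 8.4 provides for injection-site assessment through 14 days after each dose. Appendix 6 schedules a site examination about 60 minutes after each injection and again at days 98 and 154.
- The flow chart in 6.1 has a row for symptoms at every visit. Its footnote 10 is not in the available text, so it cannot be said what that row covers.

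These routes are real, but they are not equivalent to a direct question. A site reaction or headache that comes and goes between the 60-minute check and the visit two weeks later depends largely on what the patient is asked at that visit.

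**The case against.** The strongest reply is that the protocol does not leave these events to chance, for the reasons listed in the check above. A reader might infer that headache and warmth are counted only if patients volunteer them. The documents do not support that: staff ask about adverse events at every visit and inspect the site, and the unreadable footnote may say more. Section 8.6 also introduces its terms with a word that need not mean the list is complete. These points stand, and they limit the conclusion to less systematic capture.

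A reader might also try to put a number on the loss. That fails for three reasons. First, the 10% threshold has an unclear denominator: 1.2.4 can be read as a share of subjects who had a related event, and 8.2 words it differently. Second, no capture share appears anywhere in the document. Third, the reported data do not point to under-recording. In days 85 to 154, headache was recorded in 2 of 11 patients in arm 2 and 0 of 8 in arm 4, which is 2 of 19 or 10.5%, about what full capture at 10% would give (19 × 0.10 = 1.9). In days 0 to 84, headache had 6 + 5 + 2 + 2 = 15 events, against 3 + 3 + 6 + 2 = 14 for arthralgia and 3 + 4 + 2 + 2 = 11 for myalgia, both of which are solicited.

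Two further inferences should be resisted. The lack of a coded warmth term proves nothing: one vaccinee in each vaccine arm has the term local reaction, which could include warmth, and no injection-site erythema term appears either, although erythema is solicited. Nor is a bias between arms 4 and 2 shown, because 8.6 gives one list without distinguishing arms and the safety analysis is descriptive.

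Finally, nothing here shows that any discontinuation decision under 6.3.3 would have gone differently.

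**Conclusion.** The point holds in a limited form. Section 8.6 does not match 1.2.4 and 8.2: two of the eight common, patient-reportable vaccine reactions, headache and injection-site warmth, are missing from the list of direct questions. Their recording is therefore less systematic than for the other six and may be incomplete. Because adverse event occurrence is the primary outcome and headache is expected with both products, the mismatch is worth correcting. It is not evidence that events were missed, and no numerical size can be attached to it.

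The conclusion rests on two assumptions: that the 8.6 list is what staff actually ask, and that the lost footnote to the symptoms row does not already name these events. If the footnote did name headache, the headache part would shrink to an inconsistency between 8.6 and the flow chart.

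**What to change.** Reconcile section 8.6 with 8.2 by adding headache to the systemic line and injection-site warmth to the local line. The list goes from 9 terms to 11 (4 local, 7 systemic) and covers all eight patient-reportable common reactions.

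For data capture only, also add anorexia and hives, so that all seven symptoms named in 6.3.3 are asked about. That makes 13 terms (4 local, 9 systemic). The rule in 6.3.3 itself is not touched.

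State in 8.6 that the systemic items are asked in the same way in all four arms, including those that receive no vaccine.

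The cost is four more questions on an existing form and slightly higher adverse event counts. Sample size, significance level and treatment are unaffected.

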## 1.3 Rationale for the Study and Purpose

### 1.3.1 TB therapeutic vaccines as rescue therapy in MDR-TB

Vaccination with *Bacillus Calmette-Guérin* (BCG) can limit disseminated disease in children, but not the establishment of TB infection. Several prophylactic TB vaccines have demonstrated superiority to BCG in mouse models, although none of them result in sterilizing immunity (27,28). Recently, the first novel preventive TB vaccine to enter efficacy testing (MVA85A) failed with no evidence of protection against TB disease or infection (29). These disappointing data has intensified the search for correlates of protection and to identify effective vaccine measures early during development. It has become clear that the traditional clinical development with consecutive clinical trials with a final efficacy trial needs rethinking. Thus, therapeutic vaccines have been listed as an alternative approach as the study design allows to measure the biological effect of the vaccine directly e.g. by measuring bacterial loads in sputum and also open up the possibility of identifying correlates of protection. Therapeutic vaccination alone or in combination with other types of immune modulation as COX-2i may not only boost and strengthen TB immunity with possibly better outcome especially for MDR/XDR-TB, but will also significantly improve our knowledge relating to clinical study design and correlates of protection.

### **1.3.2 COX-2i improves cellular vaccine responses *in vivo***

Supported by the RCN/Global Health program we have shown for the first time in consecutive randomized clinical trials that COX-2i reduce T cell distress in HIV-1 and improve efficacy of T cell-dependent vaccines with good safety (17-19). In the study of celecoxib, antibody levels to the T cell-dependent tetanus vaccine were nearly three times higher in COX-2i-treated patients after vaccination than in controls (19). This supports our basic hypothesis that COX-2i treatment indeed can reverse T cell dysfunction in infectious diseases with a chronic inflammatory component. Furthermore, the data intriguingly suggest that COX-2i treatment could improve vaccine responses as well as improve T cell functions in general and particularly in patients with hyper-inflammatory lesions as in active TB.

### **1.3.3 COX-2i improves TB specific immune responses and regulation *in vitro***

Functional studies on the effect of COX-2i upon immune cells, longitudinally collected from clinically characterized TB patients during therapy at our hospital and from our national partners, are currently in progress in our lab. We have previously described elevated levels of Treg subsets in active and latent TB (10). In studies of active TB patients during anti-TB chemotherapy we demonstrate a decrease in the fraction of *Mtb*-specific IFN- $\gamma$ -producing T cells stimulated by TB-specific antigens (ESAT-6, CFP-10) *in vitro* already after 2 weeks of efficient treatment, whereas the pool of IL-2+ cells increased over time (30). The Treg was still able to expand after *Mtb*-specific *in vitro* stimulation, but a decline in activated Treg was seen when COX-i was added to the cells. These pilot findings indicate that COX-2i could possibly block regulatory T cells and improve TB specific immunity. In the current study these data will form the basis for additional in-depth exploratory analysis of Tregs in TB infection.

### **1.3.4 Rationale for COX-2i regimen and dose selected**

The immune modulatory effects of COX-2i are expected to be dose-dependent; hence in our previous exploratory trial of untreated HIV patients (UUSCOX2, EudraCT No 2006-001882-41, approved by the Norwegian Medicines Agency), the highest tolerated dose of celecoxib, 400 mg bid for 12 weeks (dose approved by FDA in familial adenomatous polyposis), were investigated and demonstrated improved efficacy of T cell-dependent vaccines with good safety (19). Further, we have recently ended another study of the COX-2i etoricoxib 90 mg OD given to a HIV cohort for 24 weeks (OUSCOX2, EudraCT No. 2010-020382-25) without any drug-related SAE observed.

Etoricoxib is generally well tolerated, even at doses above the clinical dose range and could be dosed once daily which is very convenient in order to secure compliance. Multiple dosing of etoricoxib up to 150 mg OD has showed no negative COX-1-mediated effects such as thromboxane B2, bleeding time or platelet aggregation (31). Steady-state pharmacokinetics of 120 mg etoricoxib, were consistent with linearity and achieved after 7 days of once-daily dosing in a study of 24 healthy subjects (32).

The COX-2i drug class has long been approved and is widely in use for inflammatory conditions. They are already in use in clinical practice for milder manifestations of immune reconstitution syndrome (IRIS), predominantly TB, in HIV-patients where they are preferred before steroids (31). The risk for cardiovascular events is low and the mechanism is still unclear as COX-2i lowers pro-inflammatory and prognostic markers of cardiovascular events in patients with CHD (32). In our last study, a number of prothrombotic factors and markers for endothelial damage were measured, finding only a slight increase of D-dimer in the control group and possibly a reduction of the pro-athrogenic cytokine IL-6 in the intervention group (19). However, also in this trial we will implement a number of exclusion criteria and patients with typical high cardiovascular risk will be excluded and parameters reflecting activated coagulation and endothelial damage will again be monitored.

The anti-TB drug rifampicin that is included in the standard regimen for TB patients recruited to this study is a CYP3A inducer in the liver and will thus reduce the serum concentration of COX-2i. Co-administration of 120 mg etoricoxib with daily doses of 600 mg rifampin resulted in a mean 65% decrease in etoricoxib AUC and 40% decrease in Cmax (33). The geometric mean ratios (etoricoxib

with rifampin/etoricoxib alone) for AUC (0-inf) and Cmax in these patients were: AUC: 0.35 (90% CI: (0.31, 0.40)), with a range of 0.25 - 0.50. Cmax: 0.60 (90% CI: (0.43, 0.84) with a range of 0.29 - 0.87). In the same individuals, the ranges of AUC's and Cmax's during rifampin treatment were as follows: AUC (0-inf) (ug\*hr/mL): 2.41-6.42 with a mean of 3.80 and SD of 1.36. Cmax (ng/mL): 362-1616 with a mean of 733 and SD of 394. Tmax for etoricoxib was not significantly altered during rifampin treatment, but the apparent terminal t1/2 (hour) was significantly different (6.8 hours with rifampin versus 14.4 hours without).

Thus, we will use Arcoxia 120 mg, the maximal dose approved (and recommended for acute arthritis urica) to overcome too low serum concentrations when co-administrated with rifampicin in TB patients. However, the serum concentration of rifampicin will not be affected and there are no interactions between COX-2i and any of the three other anti-TB drugs included in the standard regimen (isoniazide, ethambutol, pyrazinamide).

Analysis of serum-concentration of COX-2i is not routinely available and it is thus not possible to use for drug monitoring during the study. However, pharmacokinetic parameters in serum after 7 days of etoricoxib when steady state is expected (33) will be analyzed in study arm #1 in retrospect for research purposes and correlated to tolerance and immunogenicity and before inclusion of study arm #4 to achieve optimal dosing. If intolerable adverse reactions occur to etoricoxib the dose will be reduced to 90 mg or stopped.

## 2 STUDY OBJECTIVES AND RELATED ENDPOINTS

### **Primary:**

To evaluate the **safety** and **tolerability** of etoricoxib alone and in combination with the therapeutic TB vaccine H56:IC31 in patients with active TB disease treated with conventional 26-week anti-TB chemotherapy.

### **Secondary:**

To evaluate the effect of etoricoxib on i) immune regulation in TB and ii) immunogenicity to the therapeutic TB vaccine (H56:IC31) in patients with active TB disease treated with conventional 26-weeks anti-TB chemotherapy.

To investigate the pharmacokinetics of etoricoxib in TB patients treated with rifampicin.

## 3 OVERALL STUDY DESIGN

Patients admitted to the Dep. of Infectious Diseases or Dep. of Pulmonary Medicine, OUS (eventually patients admitted to other hospitals in the Oslo region and transferred to OUS or patients admitted to Haukeland University Hospital, Bergen) and with confirmed active pulmonary and/or extrapulmonary TB disease infected with drug-sensitive *Mtb* strains will be included sequentially in an open label, explorative, randomized, clinical phase I trial.

After Informed consent, inclusion, baseline assessments and before start of standard anti-TB chemotherapy (day 0-182), each patient will be randomized to the following study arms:

### **Supplementary Table 12**

| Group | Numbers | Treatment               | Endpoint                          |
|-------|---------|-------------------------|-----------------------------------|
| Arm 1 | 10      | Chemotherapy+ COX-2i    | Safety + immunogenicity           |
| Arm 2 | 10      | Chemotherapy + H56:IC31 | Safety + immunogenicity           |
| Arm 3 | 10      | Chemotherapy            | Safety + immunogenicity (control) |

|       |    |                                  |                         |
|-------|----|----------------------------------|-------------------------|
| Arm 4 | 10 | Chemotherapy + H56:IC31 + COX-2i | Safety + immunogenicity |
|-------|----|----------------------------------|-------------------------|

The study design randomizing patients will test:

1. Safety of etoricoxib and H56:IC31 alone and in combination in active TB.
2. Effect of etoricoxib on TB immunogenicity, activation and regulation (arm #1).
3. Pharmacokinetics of etoricoxib in TB patients treated with rifampicin (arm #1).
4. H56:IC31 immunogenicity after two immunizations in active TB (arm #2).
5. H56:IC31 immunogenicity after pre-treatment with etoricoxib in active TB (arm #4).

[figure not shown]

**Time-line (anti-TB chemotherapy, day 0-182)**

### Supplementary Figure 9

The safety profile of COX2i or H56:IC31 has not yet been determined in a population undergoing treatment for pulmonary TB. Therefore, we will enrol participants in two groups separated by a safety review. Group A includes volunteers for arm #1, arm #2 and arm #3 (2:2:1 randomization). First at the completion of Study Day 98 for all group A participants, the “clinical investigational group” (sponsor, PI, collaborators including representative from the H56:IC31 vaccine manufacturer) will meet and evaluate the cumulative safety data to determine if the observed safety profile meets the criteria to proceed to inclusion of volunteers for group B; arm #4 and remaining Arm #3 controls (2:1 randomization).

Arm #1 (n=10): etoricoxib treatment started at day 0 and given for 20 weeks (day 0-140) followed by 6 weeks (or according to clinical evaluation) of standard anti-TB chemotherapy alone (day 0-182) and follow-up control at day 210 and day 238.

Arm #2 (n=10): given anti-TB chemotherapy alone (day 0-182) (or according to clinical evaluation) and follow-up control at day 210 and day 238. TB vaccine H56:IC31 will be injected at day 84 and day 140.

Arm #3 (controls, n=10): given anti-TB chemotherapy alone (day 0-182) (or according to clinical evaluation) and follow-up control at day 210 and day 238.

Arm #4 (n=10): etoricoxib treatment started at day 0 and given for 20 weeks (day 0-140) followed by 6 weeks (or according to clinical evaluation) of standard anti-TB chemotherapy alone and follow-up control at day 210 and day 238. TB vaccine H56:IC31 will be injected at day 84 and day 140.

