### Secondary endpoints: immunogenicity read-outs

We used descriptive statistics (medians and IQR) to describe all pre-defined immunogenicity readouts at each study time point. In the IgG assay, we also described the number and proportion of vaccine seroconverters in each group defined as an increase in H56 IgG-responses of  $>2$ -fold from day 84 to any time point after.

Immunogenicity read-outs of primary priority for Hypothesis 1 were responses to treatment defined as the change from day 0 to day 84 in the defined outcomes (**Table 3**). The outcomes were analyzed using median regression with treatment as only independent explanatory factor. The treatment difference of the combination of both groups allocated to etoricoxib (etoricoxib-group and etoricoxib+H56:IC31-group) and the combination of controls and the H56-IC31-group (vaccine not administered until day 84) were calculated as estimated difference in median response with 95% confidence interval based on 1000 bootstrap replications and corresponding two-sided p-value. For Hypothesis 2 and Hypothesis 3, immunogenicity read-outs of primary priority were responses to vaccine treatment defined as the change from day 84 to day 154 (**Table 4 and 5**). The seed for the bootstrap replications was set to 20200316 (pre-defined as the date of the final statistical analysis plan (Version 1.0)).

Exploratory post-hoc analyses were performed for immunogenicity readouts predefined as secondary and tertiary priority from day 84 to day 154 using the same statistical analyses as for the primary priority read-outs described above.

Data were collected in the eCRF Viedoc™ version 4.66.7823.20827 and Microsoft Excel 2016. Statistical analyses were performed in STATA version 16 (StataCorp) and figures drawn in GraphPad Prism version 7.02.

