### 4.2 Number of Patients

A total of 40 patients will be included, 10 in each of the study arms.

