## 5.10 Subject Numbering and Randomization

The subjects will be included by consecutive subject numbers from 1 and upwards. Step-wise inclusion starting with Group A and proceeding with Group B if safety data are satisfactory and meet the criteria at Study Day 98 for all Group A participants.

- At inclusion day 0, the patients will be consecutively randomized (2:2:1) in groups according to study group descriptions; arm #1 on etoricoxib (n=10), arm #2 receiving H56:IC31 vaccine (n=10) and arm #3 controls (n=5).

- At inclusion day 0, the patients will be consecutively randomized (2:1) in groups according to study group descriptions; arm #4 on etoricoxib and receiving H56:IC31 vaccine (n=10 and remaining arm #3 controls (n=5).

Each subject is identified in the study by a unique subject number that is assigned when subject signs the Informed Consent Form. Once assigned the subject number cannot be reused for any other subject.

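### Enrolment part is partly confounded with treatment in two of the immunogenicity contrasts and completely in the third, because the stated model has treatment as its only factor

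*Protocol*

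**What the plan says.** Protocol section 3 (time-line text) gives the staging: "Therefore, we will enrol participants in two groups separated by a safety review". On the first part: "Group A includes volunteers for arm #1, arm #2 and arm #3 (2:2:1 randomization"). The second part comprises "arm #4 and remaining Arm #3 controls (2:1 randomization"). It opens after a safety evaluation held "First at the completion of Study Day 98 for all group A participants".

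Section 5.10 gives the first-part numbers, "arm #1 on etoricoxib (n=10), arm #2 receiving H56:IC31 vaccine (n=10) and arm #3 controls (n=5"), and says of the second part that "the patients will be consecutively randomized (2:1) in groups according to study group descriptions; arm #4" and the remaining five controls are allocated. Section 10.2 repeats the two ratios. The planned total is in section 4.2: "A total of 40 patients will be included, 10 in each of the study arms".

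Supplementary Tables 3 to 5 fix three contrasts:
- H1: arms 1+4 versus 2+3, change from day 0 to 84.
- H2: arm 2 versus 3, change from day 84 to 154.
- H3: arm 4 versus 2, change from day 84 to 154.

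The text on secondary endpoints in the detailed statistical methods specifies "median regression with treatment as only independent explanatory factor". The legends of Supplementary Figures 5 and 6 repeat this for H2 and H3. The document gives no term for part, no stratified analysis and no restriction to concurrent controls.

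**The concern.** Randomisation protects a comparison only among patients who could have been allocated to either side at the same time. Here that holds within a part, not across parts. H1 combines two parts with different odds of receiving etoricoxib (10:15 in A, 10:5 in B). H2 sets an arm recruited wholly in Part A against controls of whom half come later. H3 sets an arm wholly in Part B against an arm wholly in Part A. Section 3 nonetheless introduces the design as each patient being randomised among four arms, and nowhere says that 4 versus 2 lies outside the randomisation.

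If the change score differs between parts for reasons such as case mix, recruiting hospital or assay batch, the difference enters the treatment estimate. The protocol itself leaves routes open: section 4.1 allows further hospitals if recruitment is difficult, and section 1.3.4 has arm 1 pharmacokinetics examined before arm 4 is included. At stake is the reading of the vaccine effect, and above all of etoricoxib's adjunctive effect on the vaccine response.

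**Working it through.** **Inputs.** Planned arm sizes come from the synopsis and section 5.10, contrasts from Supplementary Tables 3 to 5, the model from the detailed statistical methods, and the two-sided 5% level from section 10.4. The between-part shift d in the change score, in SD units, is not in the document. I assume 0, 0.5 and 1.

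**1. Reproduce the planned sizes.** Part A: 25 × (2/5, 2/5, 1/5) = 10, 10, 5. Part B: 15 × (2/3, 1/3) = 10, 5. Total 25 + 15 = 40, ten per arm, with controls split 5 + 5. This agrees with the protocol.

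**2. Share enrolled in Part B, and bias.** Bias = (share on first side − share on second side) × d.

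| Contrast | First side | Second side | Bias |
|---|---|---|---|
| H1: 1+4 vs 2+3 | 10/20 = 50% | 5/20 = 25% | 0.25d |
| H2: 2 vs 3 | 0/10 = 0% | 5/10 = 50% | −0.50d |
| H3: 4 vs 2 | 10/10 = 100% | 0/10 = 0% | 1.00d |

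For H1 and H2 the formula is exact for means and approximate for medians. Simulated average median differences at d = 1 were 0.27, −0.52 and 1.00.

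**3. Can a covariate repair H3?** No. With intercept, arm and part, the design matrix for arms 2 and 4 has three columns and rank 2. Arm and part are the same variable.

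**4. Rejection rate with no treatment effect.** Simulated difference in medians divided by its bootstrap SE, compared with 1.96 (2,000 trials, 500 resamples, normal data with SD 1).

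| Contrast | d = 0 | d = 0.5 | d = 1 |
|---|---|---|---|
| H1 | 5.8% | 5.8% | 7.5% |
| H2 | 4.6% | 6.9% | 13.7% |
| H3 | 6.3% | 16.2% | 44.4% |

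Monte Carlo error near 5% is √(0.05 × 0.95 / 2000) ≈ 0.5 percentage points, so H1 shows no detectable inflation at d = 0.5.

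**5. Precision cost of within-part comparison (mean scale, SD units).**
- H1 unadjusted: √(1/20 + 1/20) = 0.316. Within-part information is 10 × 15/25 = 6.00 in A and 10 × 5/15 = 3.33 in B, so the stratified SE is 1/√9.33 = 0.327, or +3.5%.
- H2: √(1/10 + 1/10) = 0.447 with all controls; √(1/10 + 1/5) = 0.548 with Part A controls, or +22%.
- H3: 0.447 direct. Bridged through controls, √(1/10 + 1/5 + 1/10 + 1/5) = 0.775, and the variance ratio is 0.6/0.2 = 3.

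**6. Baseline.** In Supplementary Table 7, two or more symptoms occur in 9/12 of arm 2 and 1/8 of arm 4 (Fisher p about 0.02). A BCG scar occurs in 5/12 and 6/8 (p = 0.20).

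**The case against.** The best defence is context. The primary objective is safety, reported without testing between arms. The immunogenicity endpoints are secondary. The legend of Supplementary Figure 3 treats p-values as supporting hypotheses rather than confirming them, and section 10.4.6.1 disclaims formal hypothesis testing. Staging is a disclosed safety measure, and controls were placed in both parts. Outcomes are within-patient changes, so drift in level cancels. The statistical analysis plan is not at hand and may hold a sensitivity analysis.

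Much of this stands, and it limits the weight of any argument from false-positive rates. It does not remove the point. Supplementary Tables 3 to 5 do speak of formal testing, which needs reconciling with section 10.4.6.1. Bias in an estimate and its interval does not depend on what the p-value is called. Change scores remove drift in level, not drift in the change. The objection is to the analysis and its description, not to staging.

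A reader might infer more than the document supports:
- **That drift occurred.** The symptom difference is one row picked from a long table in small groups. It matters only if it predicts change, which nothing shows, and the actual A/B split of controls is not reported.
- **That H3's error rate reaches 61% at a 1 SD shift.** That follows from a normal test of means. For the median difference the simulation gives 44.4%.
- **That all three contrasts are equally affected, or all pool the parts.** H1 and H2 are partly confounded. H3 pools nothing; it compares one part with the other.
- **That Part B waits until Part A is finished.** The gate is day 98, while follow-up runs to day 238.
- **That sections 10.1 and 10.2 hide the control split.** Section 10.2 states the staged recruitment, and the ten per arm in 10.1 refers to other vaccine studies. Neither needs correcting.

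**Conclusion.** The point holds. The stated analysis leaves enrolment part partly confounded with treatment in H1 and H2 and fully aliased with it in H3. The bias is about 0.25, 0.5 and 1.0 times any between-part shift in the change score. H3 carries most of the concern and H2 comes next; the effect on H1 is modest.

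The shares use planned sizes. The full analysis set was 10, 12, 10 and 8 for arms 1 to 4, so they are approximate for H1 and H2, while H3 stays at 100% versus 0% if the staging was followed. The rejection rates rest on assumed shifts and normal data. The SE costs are on the mean scale, not that of median regression. The size of d, including whether it is zero, cannot be learned from the document.

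**What to change.** 1. **H1:** fit part (A/B) as a stratum. Cost: about 3.5% on the mean-scale SE.
2. **H2:** report arm 2 against concurrent Part A controls beside the comparison with all controls. Cost: the mean-scale SE of the concurrent estimate rises from 0.447 to 0.548 SD, with five controls.
3. **H3:** state that arm 4 versus arm 2 is a non-randomised comparison between parts. This costs nothing. Optionally, show as a sensitivity analysis (arm 4 minus Part B controls) minus (arm 2 minus Part A controls), noting that it triples the variance, rests on five controls per part and assumes no treatment-by-part interaction.
4. **Wording:** reconcile section 10.4.6.1 with the testing language of Supplementary Tables 3 to 5, and amend the sentence in section 3 that presents a single randomisation to four arms.

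No new data are needed, only each patient's part, which the randomisation records already determine.
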